### Randomization and blinding

After retrieval of written informed consent and baseline data, participants will be allocated to the intervention group or to the control group, stratified by professionals and volunteers (Fig. 1). To ensure a close balance of entities in each group, randomization will be performed by randomly selected block sizes of four and six. The randomization list will be computer generated by a scientist who is not involved in either the intervention or data collection. An independent person will also perform the allocation. As safeguards, no other person will have access to the list, and the list will be sent by e-mail only in an encrypted format.

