### Outcomes

The primary outcome measure is *knowledge*, which is operationalized as an understanding of decision-making processes in healthcare affairs and in setting realistic expectations regarding probabilities of benefits and harms of PEG, PR and AP to people with dementia.

Secondary outcome measures are: 1) legal representatives have obtained sufficient knowledge (using a cut-off of 70% correct answers in the knowledge test); 2) legal representatives have obtained sustainable knowledge, which is measured 6 months after intervention; 3) percentage of persons concerned affected by PEG, FEM or AP during follow up of 6 months; and 4) result of the first decision after intervention regarding PEG, PR and AP for the persons concerned including time to first decision.

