### Data collection

In the T0 baseline, data of legal representatives will be assessed according to age, gender, education status, activity status (professional or voluntary representative), time since appointment as legal representative and number of persons concerned. Additionally, baseline data and baseline outcome measurements of persons concerned will be assessed. For this, legal representatives will receive a pseudonymization list, documentation sheets and a standardized written introduction. A pseudonymization number will be assigned to each person concerned with dementia. All data will be given to the study site under this pseudonym. The legal representative, using data extracted from routine documentation, will fill in the documentation sheets. The age range, gender, diagnosis additional to dementia, presence of PEG, number and types of PR, name and dosage of antipsychotics will be assessed by multiple choice and free-response questions. Copies of the routine documentation (e.g., a list of drug prescriptions) will be passed on only if pseudonymization is safeguarded.

At T1, the primary outcome *knowledge* will be assessed (Table 1). To assess understanding and realistic expectations, a novel questionnaire was developed based on Bloom’s taxonomy [40], the *User Manual–Realistic Expectations* [41], the contents of the education program, and the evidence-based information for PEG, PR and AP in people with dementia. The questionnaire comprises 13 items: two items on the understanding of decision-making processes in healthcare affairs; two items on quality and validity of study results; and nine items on realistic expectations regarding probabilities of benefits and harms of PEG, PR and AP to people with dementia (with three items per intervention). All items are multiple choice questions with four choices, with only one correct answer. Questions with more than one answer and unanswered questions will count as a wrong answer. No summarizing score is given if four or more of the 13 questions remain unanswered.

**Table 1 Tab1:** Data collection

Outcomes	Measures	Follow-up
Knowledge	Questionnaire developed on the basis of evidence-based information and contents of the education program	T1, T3
First decision PEG	Standardised telephone interview	T2, T3
First decision PR	Standardised telephone interview	T2, T3
First decision AP	Standardised telephone interview	T2, T3
Physical restraints	Documentation sheet; medical and nursing records	T3

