### Data analysis

Data will be entered into a SPSS database and double-checked by student assistants blinded to the group allocation. Simple plausibility checks will be done in the study center before the final statistical analysis by the statistician. Analysis of all quantitative data will use the intention-to-treat principle. Missing values in primary and secondary outcomes will be imputed using simple methods. A dropout analysis comparing baseline parameters between the study population and early dropouts (before T2) will be performed.

All statistical tests are two-sided using a significance level of 5%. Baseline parameters are described by frequency tables, means, standard deviations or quartiles.

The primary outcome is the percentage of correct answers for the knowledge test at T1. Assuming approximate normal distribution, the expected values from the IG and CG will be compared with adjustment for stratified randomization by professionals and volunteers using bifactorial analysis of variance (linear model). Distribution assumptions will be investigated by graphical methods. Furthermore, interactions between intervention and professional status will be included in a secondary model. Different effects depending on the professional status will be discussed.

The secondary outcome of sufficient knowledge (binary) at T1 will be compared between IG and CG using bivariate logistic regression, including IG/CG and professional status as independent variables. Additionally interactions between intervention and professional status will be investigated in a second model.

The sustainability of knowledge will be investigated at T3. The time course of the knowledge between T1 and T3 will be analyzed by fitting a linear mixed model: the dependent variable is knowledge (% of correct answers), and the independent variables are IG/CG, time (T1, T3), interaction between intervention and time, professional status and interaction between intervention and professional status. To adjust for repeated measurements of the legal representatives, random effects are included (covariance pattern model with covariance structure compound symmetry).

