Further secondary outcomes are the numbers of persons concerned and the percentage of these persons affected by PEG, FEM or AP (separately) per legal representative at T3. Mean values ± standard deviations will be described for IG and CG at T3 as well as at T0. Linear models will be fitted including IG/CG and initial values at T0 as independent variables.

Finally, the results of the first decision about PEG, FEM or AP by the legal representative after T0 (e.g., after training for IG, or after randomization for CG) will be assessed. Initially, the duration from T0 to the first decision will be described for IG and CG by Kaplan-Meier curves. In case of no decision, durations are censored at the end of observation after 6 months or at dropout. Kaplan-Meier curves between both groups will be compared by the log rank test, as long as there are no clear deviations from the proportional hazard assumption in the graphics. Four categories of decisions will be described by frequency tables.

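### First decisions count from training in the intervention group but from randomisation in the control group, while duration runs from T0, so the log-rank comparison lacks one defined time origin

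*Protocol article*

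**What the plan says.** The Outcomes section lists as the fourth secondary outcome the "result of the first decision after intervention regarding PEG, PR and AP for the persons concerned including time to first decision". Under Data analysis, the decisions that count are those "after T0 (e.g., after training for IG, or after randomization for CG) will be assessed". The following sentence sets the clock: "Initially, the duration from T0 to the first decision will be described for IG and CG by Kaplan-Meier curves". Censoring reads: "In case of no decision, durations are censored at the end of observation after 6 months or at dropout". The test follows: "Kaplan-Meier curves between both groups will be compared by the log rank test", provided that the graphs show no clear departure from proportional hazards.

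T0 has a meaning elsewhere. Data collection uses it for the baseline assessment ("In the T0 baseline, data of legal representatives will be assessed according to age"), and Randomization and blinding puts allocation after that step: "After retrieval of written informed consent and baseline data, participants will be allocated to the intervention group or to the control group". Training comes later still, in scheduled group courses of six to ten people. The length of the wait is not given. Data analysis also states: "Analysis of all quantitative data will use the intention-to-treat principle".

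**The concern.** The rule names a different starting event for each arm and then uses a single symbol, T0, for the clock. The text allows two readings.

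- **T0 is baseline in both arms.** Between T0 and the course, a decision in the CG is an event and a decision in the IG is not. The IG carries time in which it cannot fail (immortal time).
- **T0 is reset by arm**, to training in the IG and randomisation in the CG. The immortal time disappears, but the two clocks start at different stages. IG decisions made while waiting are dropped, and an IG member who never attends has no start date.

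The definition under Outcomes does not settle it: a first decision after intervention has no natural start in the CG, which is offered the course only after follow-up.

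At stake is the only time-to-event comparison of real decisions in the trial. The same counting rule also determines which decisions enter the frequency tables of the four decision categories.

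**Working it through.** **Plan's own figure.** The article gives no figure for this outcome. The arm sizes come from the primary-outcome calculation, which reproduces. The normal approximation gives n = 2 × (1.960 + 1.282)² × (0.17/0.085)² = 84.1, so 85. The t-test solution is 85.03, so 86 per group. With 20% dropout, 86/0.8 = 107.5, so 108 per group and 216 overall.

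**Inputs from the article.** Two arms 1:1, 108 randomised or 86 analysed per arm, follow-up of 6 months (26 weeks), two-sided 5% log-rank test.

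**Assumptions, because the article is silent.** Wait L from T0 to training of 2, 4 or 8 weeks; proportion P deciding within 26 weeks of 10%, 30% or 50%; one record per representative; constant hazard; no dropout; no true effect.

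**Reading 1: clock from baseline, IG events only after training.** The hazard is λ = −ln(1 − P)/26 per week. For P = 50%, λ = 0.6931/26 = 0.0267.

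Share of the CG with an event during the wait, 1 − (1 − P)^(L/26):
- P = 50%: 5.2%, 10.1% and 19.2% for L = 2, 4 and 8 weeks.
- P = 30%, L = 8: 10.4%.
- P = 10%, L = 8: 3.2%.

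In the IG this share is zero by construction. By week 26 the IG shows 1 − exp(−λ(26 − L)) deciding. For P = 50% that is 47.3%, 44.4% and 38.1%, against 50% in the CG.

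Simulated type I error of the log-rank test, 108 per arm:

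| Deciding within 26 weeks | Wait 2 weeks | Wait 4 weeks | Wait 8 weeks |
|---|---|---|---|
| 10% | 5% | 8% | 14% |
| 30% | 7% | 11% | 34% |
| 50% | 9% | 20% | 62% |

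Repeat runs agree to within about two percentage points. With 86 per arm the errors are somewhat lower: 6.3/9.7/27.2% at P = 30% and 6.9/17.8/51.1% at P = 50%. At P = 50% the spurious hazard ratio (IG to CG) is about 0.90, 0.80 and 0.64. From a 4-week wait at P = 30% or more, nearly all rejections show the IG as slower.

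**Reading 2: clock reset to training in the IG.** With a constant hazard, 108 per arm and P = 50%, the error is about 5% and the hazard ratio about 1.00. If the hazard is doubled in the first 4 weeks after baseline (an assumption) and the wait is 4 weeks, the error is about 17 to 18% and the hazard ratio about 0.83. An early rise is conceivable: the baseline forms ask each representative to record PEG, restraints and antipsychotics for every person concerned, and any consideration of these counts as a decision.

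**One origin and one counting rule in both arms.** Across the scenarios simulated, the error is 4.4 to 5.9% and the rate ratio about 1.00.

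**The case against.** The strongest reply is that the parenthesis simply explains what T0 means for this outcome. Outcomes speaks of decisions after the intervention, T1 is defined relative to the intervention, the CG receives its T1 test in parallel with the IG, and decision sheets are issued at the start of follow-up without distinction by arm. On that reading there is no immortal time. This stands as a possible reading, so a reader who infers that immortal time is certain goes further than the text. It does not rescue the rule. No section sets the CG start for decisions to the course date, the parenthesis itself puts it at randomisation, and T0 would then have two meanings.

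The size depends on assumed inputs. This stands. Decisions are recorded separately for the three interventions, and the Background puts PEG prevalence at 5%, so 50% deciding may be high for PEG. At 10% deciding and a 2-week wait the error is nominal. The 62% figure needs an 8-week wait, 50% deciding and no dropout.

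The proportional-hazards proviso might stop the test in the extreme cases, where the IG curve is flat while about 19% of the CG have events. The simulated figures are therefore for the log-rank test alone, not for the test plus a visual check. The check cannot correct a wrong origin, and a 2- to 4-week lag may pass unnoticed.

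Two further inferences are tempting. One is that the artefact would be credited to the programme. It makes the IG look slower, and the Objectives state no hypothesis that training delays decisions, so it could equally mask faster decisions. The other is a flat contradiction of intention to treat. No section excludes non-attenders or reassigns anyone. The tension is limited to IG decisions dropped before training and to non-attenders without a start date.

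**Conclusion.** The concern holds as a defect in the stated rule. The arms have different starting events, and the clock runs from a T0 that elsewhere is the pre-randomisation baseline. On the baseline reading, the log-rank test is biased towards slower decisions in the IG. The type I error runs from about nominal (2-week wait, 10% deciding) to about 62% (8-week wait, 50% deciding). On the reset reading, the error is nominal under a constant hazard, but the comparison is exposed to any early change in the decision rate after baseline. All these sizes rest on an assumed wait and decision rate.

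The point affects secondary outcome 4 only and should be fixed. It does not threaten the primary outcome or the sample size, and a more serious grading is not supported.

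**What to change.** Use one origin and one counting rule in both arms, neither depending on attendance. The index date is the scheduled end of the course for which the participant registered; for the CG this is the date on which the T1 test is sent in parallel with the IG. Count the first decision after that date in both arms, include IG members who did not attend, and censor both arms 6 months later. Apply the same rule to the frequency tables of decision categories, and keep T0 for the baseline assessment only.

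Add a sensitivity analysis from the randomisation date only if decision sheets are issued at randomisation in both arms. The article issues them at the start of follow-up, so IG decisions made during the wait may not be recorded.

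The main change costs a revised sentence or two and one index date per participant, since decision dates are already documented. The sensitivity analysis costs an earlier issue of the sheets.

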Additionally, the number of PEG, PR and AP interventions in the persons concerned will be assessed (Table 1). The legal representatives will perform the assessment as at T0, filling out the documentation sheets and forwarding any copies of routine documentation. New diagnoses since baseline, the presence of PEG, the number and types of PR, medication data and decisions made about one of these interventions will be documented.

All persons concerned who are represented by one of the participating legal representatives at least for 2 weeks within the 6-month follow-up are eligible. If a person concerned who was assessed at T0 is no longer represented by the participant prior to end of follow-up, a documentation sheet will be filled out. The time of and reason for dropout, as well as the presence of PEG, number and types of PR and medication data at the time of dropout, will be documented. New persons concerned during the study period will be assessed at the time of inclusion and at T3. At the time of inclusion, a documentation sheet will be filled out, including time of inclusion, age range, gender, any diagnoses additional to dementia, the presence of PEG, number and types of PR and medication data.

Participants will receive the knowledge test and documentation sheets by mail or, if requested, by email. Participants in the CG have to submit the documents before subsequently beginning the education program (they may hand them over in person on the first training day).

Participants who had not made all three decisions regarding PEG, PR or AP for a person concerned at T2 will be additionally contacted by phone and asked again if they had made a decision since T2. Results of the first decision of each intervention will be recorded as in T2.

To reach a high compliance rate until T3, participants will receive stamped, addressed envelopes for returning outcome assessments by mail. Submission of all documents to the study center will be also possible by email or fax. If required, participants will be reminded by phone, and any of their questions about data assessment will be answered.

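### Time to first decision: censoring at dropout does not separate study withdrawal from end of representation, so the Kaplan-Meier curves can overstate the proportion who decide

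*Protocol article*

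**What the plan says.** The Data analysis section states that "the duration from T0 to the first decision will be described for IG and CG by Kaplan-Meier curves". Where no decision was made, "durations are censored at the end of observation after 6 months or at dropout". For the group comparison the section says that "Kaplan-Meier curves between both groups will be compared by the log rank test", provided the plots show no clear departure from proportional hazards. No reason for dropout is distinguished and no competing event is named.

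Two related matters are left open.

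- **The unit.** Data analysis speaks of "the results of the first decision about PEG, FEM or AP by the legal representative after T0". The Outcomes section defines the endpoint as "result of the first decision after intervention regarding PEG, PR and AP for the persons concerned including time to first decision", and Data collection arranges a further telephone contact for "Participants who had not made all three decisions regarding PEG, PR or AP for a person concerned at T2". The first points to the representative, the other two to the person concerned.
- **The meaning of dropout.** The Sample size section applies the word to randomized representatives (at most 20%), and the dropout analysis under Data analysis reads the same way. Data collection applies it to persons concerned: "If a person concerned who was assessed at T0 is no longer represented by the participant prior to end of follow-up", then a sheet is completed. What it captures is "The time of and reason for dropout, as well as the presence of PEG, number and types of PR and medication data at the time" when representation ended.

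**The concern.** Kaplan-Meier treats a censored subject as someone who could still have the event later, at the same rate as those who remain under observation. That is a conventional assumption for a representative who withdraws from the study, since that representative goes on making decisions unseen.

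It does not describe a person whose representation has ended. That representative can no longer decide anything for that person, so the event has been ruled out and not merely left unobserved. Censoring such a person shares out their probability among those still represented, and the curve then answers what would happen if nobody ever left.

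At stake is how the curves are read. A reader will take the six-month value of one minus Kaplan-Meier as the share in whom a decision was made. Where exits of the second kind are censored, that share is too high.

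**Working it through.** **Plan's own figure.** The article states no decision probability, exit rate or power for this outcome, so there is nothing to reproduce. Its one computed figure, the sample size for the knowledge test, has no bearing here.

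**Inputs.** All are assumptions, because the article gives none of them:

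- p = six-month value of one minus Kaplan-Meier: 20, 40, 60, 80%.
- q = probability of an exit that rules out a decision within six months: 5, 10, 20%.
- Constant, mutually independent hazards over six months.

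**Formulas.** Decision hazard l = −ln(1 − p) and exit hazard m = −ln(1 − q), per six months. The proportion who actually decide is the cumulative incidence

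CIF = l/(l + m) × [1 − exp(−(l + m))] = l/(l + m) × [1 − (1 − p)(1 − q)].

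The overstatement is p − CIF.

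**Worked case, p = 40%, q = 10%.** l = 0.511 and m = 0.105, so l/(l + m) = 0.829. The bracket is 1 − 0.6 × 0.9 = 0.46. CIF = 0.829 × 0.46 = 0.381, an overstatement of 1.9 points.

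**Range.** Each cell gives CIF, with the overstatement in percentage points in brackets:

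| p | q = 5% | q = 10% | q = 20% |
|---|---|---|---|
| 20% | 19.5% (0.5) | 19.0% (1.0) | 18.0% (2.0) |
| 40% | 39.1% (0.9) | 38.1% (1.9) | 36.2% (3.8) |
| 60% | 58.7% (1.3) | 57.4% (2.6) | 54.7% (5.3) |
| 80% | 78.5% (1.5) | 77.0% (3.0) | 73.8% (6.2) |

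**Each intervention separately.** Table 1 lists first decisions for PEG, PR and AP on separate lines. If the curves are drawn that way, p may be low. With q = 10% and p = 5, 12.5 and 30%, the overstatement is about 0.25, 0.6 and 1.4 points.

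**Representative as the unit.** A decision becomes impossible only when every represented person is lost and none is newly taken on. With independent loss of 10 to 20% per person and k persons, the probability that all are lost is q^k:

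- k = 1: 10 to 20%
- k = 2: 1 to 4%
- k = 3: 0.1 to 0.8%

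At p = 40%, an exit probability of 4% gives 0.511/0.552 × (1 − 0.6 × 0.96) = 0.393, an overstatement of about 0.7 points. That is the upper end for two persons; for three or more it is smaller still. Persons newly taken on reduce it further.

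**The case against.** The strongest reply is that the censoring sentence concerns decisions by the legal representative, who is the randomized participant, and that the Sample size section uses dropout for representatives. On that reading the plan censors someone who leaves the study but can still decide, which is ordinary practice. The use of dropout for a person concerned sits among the rules for the documentation sheets and not in the decision analysis. This stands to the extent that a reader cannot infer from the text that the curves will be biased. It does not dispose of the point. Outcomes and Data collection tie the decision to the person concerned, one person with dementia is enough for eligibility, and one word covers both kinds of exit.

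Other stronger readings also go further than the document does:

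- **Death.** A reader might infer that deaths drive the exits. Death is not named anywhere in the article. The argument needs only that representation ended, for whatever reason.
- **Decision rates from the Background.** A reader might use the prevalences there (5% PEG, 12.5% PR, almost 30% AP). These are prevalences among nursing home residents, not six-month decision rates. The article counts any consideration as a decision, even one that changes nothing.
- **A distorted group comparison.** If exits differed by arm, the gap between the curves would shift as well, but nothing in the article suggests that they do. The log-rank test remains a valid comparison of cause-specific hazards if other censoring is independent.

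It can also be said that a condensed article leaves competing events to the analysis plan. Here, however, the censoring rule is stated, and it is that stated rule which needs to be divided.

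**Conclusion.** The point holds conditionally. The stated rule merges a censoring event with an event that rules out the outcome. Where the unit is the person concerned, or a representative whose only person is no longer represented, one minus Kaplan-Meier overstates the proportion reaching a decision.

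The direction follows from the method. The size rests wholly on assumed rates: about 0.5 to 6 points across the range shown, towards the lower end if each intervention is analysed separately at low decision rates, and negligible for representatives with several persons. The share of representatives with a single person is not given.

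The planned test survives as a cause-specific comparison, and the primary knowledge analysis is not affected. Since the outcome is secondary and largely descriptive, this is a minor priority.

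**What to change.** In the Data analysis section:

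1. State whether the unit is the representative or the person concerned, and what dropout means for this outcome.
2. Treat end of representation as a competing event. If the analysis is per representative, this means end of representation of the last person concerned with none newly taken on.
3. Show Aalen-Johansen cumulative incidence curves of first decision by arm in place of one minus Kaplan-Meier.
4. Censor only at withdrawal or loss of contact of the representative and at the six-month end.
5. Keep the log-rank test, labelled as a comparison of cause-specific hazards.

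The cost is a few sentences and a standard procedure. For persons assessed at T0, Data collection already records when and why representation ended. For persons who join later, the article describes sheets at inclusion and at T3 only, so the team should check that an earlier exit is recorded in the same way. The downside is slightly lower reported decision percentages.

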## Methods/design

### Design

The PRODECIDE-RCT is a randomized controlled superiority trial with two parallel groups, a 1:1 randomization and a six-month follow-up. Together with the trial, qualitative methods will be used to achieve in-depth understanding of the implementation processes. Additional e-learning modules will be developed and tested for usability.

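### The T3 linear models for persons concerned and the log-rank test omit the randomisation stratum (professional or volunteer): if status is prognostic, power is lost for no gain; minor

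*Protocol article*

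**What the plan says.** Under Randomization and blinding, "participants will be allocated to the intervention group or to the control group, stratified by professionals and volunteers", and "randomization will be performed by randomly selected block sizes of four and six".

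The Data analysis section treats status in two ways.

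- **Knowledge outcomes.** The primary comparison at T1 is "compared with adjustment for stratified randomization by professionals and volunteers using bifactorial analysis of variance (linear model". The logistic model for sufficient knowledge and the T1/T3 mixed model for knowledge also contain professional status.
- **Other secondary outcomes.** For the number of persons concerned and the percentage with PEG, PR (written FEM there) or AP at T3, "Linear models will be fitted including IG/CG and initial values at T0 as independent variables". For time to first decision, "Kaplan-Meier curves between both groups will be compared by the log rank test, as long as there are no clear deviations" from proportional hazards in the plots. Neither sentence mentions status, and no other section brings it back.

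**The concern.** The article adjusts the primary comparison expressly because the randomisation was stratified, then drops that factor where the outcome concerns the persons represented. Stratified blocks remove nearly all chance imbalance in status between the arms. An analysis that ignores status still counts the variation due to status as noise, so its standard error is too large whenever status predicts the outcome. The test then rejects a true null less often than 5% and has less power than the design could give.

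This matters because reducing PEG, PR and AP is a stated further objective, while the sample size was set for knowledge alone. For time to first decision there is a plausible route. The clock stops at the representative's first decision, any consideration counts as a decision, and each additional person represented is another chance of an early one. If professionals represent more people with dementia, they would tend to decide sooner.

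A secondary point sits in the same sentence. The log-rank test is made conditional on how the observed curves look, so whether this outcome is tested at all depends on the data.

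**Working it through.** **1. The plan's own figure.** Inputs from Sample size: SD 0.17, difference 0.085, two-sided 5%, power 90%. The normal formula gives 2 × (1.960 + 1.282)² × (0.17/0.085)² ≈ 84.1, so 85 per group. The t-test solution is 85.03, so 86 per group (172 overall). Dropout: 86/0.80 = 107.5, so 108 per group, 216 in all. The stated figures reproduce. They concern the primary outcome only; no power is stated for the analyses discussed here.

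**2. Linear models.** Let R² be the share of outcome variance, after T0 adjustment, that status explains. Under stratified allocation the test that ignores status has

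- true size = 2 × [1 − Φ(1.960/√(1 − R²))];
- power = 1 − Φ(1.960/√(1 − R²) − (1.960 + 0.842)), where the adjusted test has 80%.

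At R² = 0.10, 1.960/√0.90 = 2.066. The size is 3.9% and the power is 1 − Φ(2.066 − 2.802) = 76.9%.

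| Residual R² (assumed) | 0 | 0.01 | 0.05 | 0.10 | 0.20 |
|---|---|---|---|---|---|
| True size, % | 5.0 | 4.9 | 4.4 | 3.9 | 2.8 |
| Power as written, % (adjusted: 80) | 80.0 | 79.7 | 78.5 | 76.9 | 72.9 |

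A simulation with 172 representatives, blocks of 4 and 6, and a T0 coefficient of 0.7 agrees. A status shift of 0.5 in the outcome but not in T0 gives residual R² = 0.0625/(0.0625 + 0.51) = 0.109, and power of 77.1% without status against 80.5% with it. When status shifts only the T0 value, power is 80.7% against 80.8%: no loss.

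**3. Log-rank test.** Two simulated set-ups, both with exponential times, a 50:50 mix of professionals and volunteers, and censoring at six months. All rates are assumptions.

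- **A:** 172 representatives, blocks of 4 and 6, volunteer hazard 0.1 per month (1 − e^(−0.6) = 45% decided by six months), treatment hazard ratio 1.6.
- **B:** 108 per arm, 30% of control volunteers decided by 26 weeks, treatment hazard ratio 1.5.

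| Professional:volunteer hazard ratio | A: size unstratified, % | A: power unstratified / stratified, % | B: power unstratified / stratified, % |
|---|---|---|---|
| 1 | 4.6 | 62 / 62 | 42.6 / 42.6 |
| 1.5 | 5.2 | 66 / 67 | 45.8 / 46.8 |
| 2 | 4.4 | 66 / 70 | 49.3 / 51.8 |
| 3 | 3.2 | 62 / 74 | 53 / 61 |
| 5 | 1.5 | 49 / 76 | 42 / 64 |

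The stratified test has size of about 5% throughout. The 5.2% is within simulation error: with 10,000 trials the standard error is √(0.05 × 0.95/10,000) = 0.2 points. Losses are therefore 0, about 1, 2 to 5, 8 to 12 and 22 to 27 points. With unequal strata they shrink: with 69 professionals and 17 volunteers per arm, the loss at a status hazard ratio of 3 is about 5 points.

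**4. The condition on curve shape.** The log-rank test is valid under the null of equal curves without a proportional hazards assumption. Non-proportionality affects its power and the meaning of a single hazard ratio, so the condition does not protect the error rate. The two points also interact. Pooling strata with different hazards can make the pooled hazard ratio drift over time even when hazards are proportional within each stratum, so leaving status out could itself trigger the condition.

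**The case against.** The strongest reply has four parts.

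- **The log-rank part rests on silence.** The article does not rule out stratification, and a full analysis plan, not shown here, could specify it or name a fallback for non-proportional hazards. This stands, and the absence of a named alternative is not held against the article. It does not cover the linear models, whose covariates are listed, nor the condition on curve shape, which is stated.
- **The T0 value already does much of the work.** This stands, and it is why the linear-model loss is small. The number of persons concerned is the outcome most likely to differ in mean by status, but its T0 value is in the model.
- **Differing spread is not the mechanism.** A reader might infer that percentages are noisier for representatives of one person than of many, and that this makes the linear models conservative. It does not; only a difference in stratum means beyond T0 does. With equal mean prevalence of 30%, eight persons per professional and one per volunteer, 43 of each per arm and T0 adjusted, simulated size was 5.1% both with and without status.
- **Large log-rank losses need strong assumptions.** A reader might take status hazard ratios of 3 or more as given. The article has no caseload or decision rate by status and no stratum mix, so the range has to start at no loss.

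**Conclusion.** The inconsistency is real: the factor that stratified the randomisation is in every knowledge model but is absent from the T3 linear models for persons concerned and interventions, and from the log-rank test as described. The consequence is conditional. If status is prognostic (beyond the T0 value, for the linear models), these secondary tests are somewhat conservative and lose power.

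The linear-model loss is probably 0 to about 3 points (residual R² up to 0.10). The log-rank loss runs from nothing to 22 to 27 points as the status hazard ratio goes from 1 to 5 under a 50:50 mix, and is smaller if the strata are unequal. Every one of these figures rests on assumed prognostic strength, which the article does not supply.

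Two stronger readings are not supported. The p-values are not invalid: the true error rate stays at or below about 5%. Nor does the point reach the knowledge analyses: the T3 knowledge model includes status, and the primary comparison and its sample size are unaffected. Making the log-rank test conditional on the look of the curves is a real but secondary point. Severity: minor, a free improvement.

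**What to change.** - Add professional status as a covariate, beside group and T0 value, to each T3 linear model for the number of persons concerned and the percentage with PEG, PR or AP.
- State that the log-rank test for time to first decision is stratified by professional status, and give a stratified Cox hazard ratio with it.
- Remove the condition on curve shape and report the stratified log-rank test in every case. If hazards look non-proportional, say so when interpreting the hazard ratio.

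The cost is a sentence or two of analysis wording. Status is already recorded at T0 and used for allocation, so no new data are needed. If status turns out not to be prognostic, nothing material is given up: at a status hazard ratio of 1 the power was 42.6% with and without stratification.
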